### Procedure and Randomization

Potentially eligible participants (and their parents) can receive oral, written, and/or online information about the study. In the Canadian provinces involved in this study, there is no specified age of consent. A minor’s ability to consent or assent is decided after assessing capacity to consent. In this study, 15 to 17 year-olds will be allowed to consent to the study on their own behalf. We will require parental consent for adolescents aged 13 to 14 years. This decision was not based on any age of consent law; we want to acknowledge the role that parents have in their younger adolescent’s activities and their ability to provide perspective on their child’s potential participation in the study. Requiring parental consent will provide us with a formal mechanism to engage with parents before study enrolment. We will seek assent from adolescents aged 13 to 14 years even if they were assessed as being able to consent.

Randomization takes place after informed consent/assent is obtained. Adolescents are randomly assigned using a computer-generated allocation sequence. Participants are randomly allocated to one of two treatment conditions and receive this allocation information via e-mail from a graduate student trainee affiliated with the project. The e-mail also provides login/website information to the allocated intervention. Given the study objectives, the pilot was designed as open-label.

### Measures

#### Primary Outcome Measure

Change in anxiety symptoms in adolescents will be measured using the total score from the Multidimensional Anxiety Scale for Children (MASC2; 50 items). The MASC2 is one of the most widely used self-report measures in clinical trials in adolescents with anxiety disorders. It assesses physical symptoms, social anxiety, harm avoidance, separation/panic, and total anxiety, and has excellent 3-month test-retest reliability [40] and excellent validity [41,42]. Adolescent self-report is desirable because of the internalizing nature of anxiety [43]. The MASC2 is administered online via Intelligent Research Intervention Software (IRIS) to adolescents in the treatment group at three data collection time points: baseline (pre-treatment), 8 weeks/end of 8^th^
*Breathe* module (post-treatment) and 3 months post-treatment (follow-up). Adolescents in the control group complete the MASC2 at baseline and 8 weeks after study enrolment via IRIS. Table 1 outlines screening and outcome measurement time points.

**Table 1 table1:** Outcome measurement schedule.

	Study time points					
	Study eligibility screening	Baseline	8 weeks (postintervention)	20 weeks (3-month follow-up)	End of study enrolment period (22 months from trial start)	End of data collection period (27 months from trial start)
Demography	X					
SCARED	X					
ASQ	X					
Co-intervention use/costs			X			
MASC2		X	X	X		
MCID			X			
Treatment satisfaction			X			
Treatment adherence			X			
Number of adolescents screened					X	
Number of adolescents enrolled					X	
Number of adolescents retained at 3-month follow-up						X

#### Secondary Outcome Measures

All secondary outcome data are collected via self-report using IRIS. The MCID will be determined for the primary outcome measure following module 8 completion (post-intervention). Adolescents allocated to the treatment condition are asked to indicate the minimum change in anxiety for which they would consider treatment participation. We will use the MCID to guide interpretation and application of outcome change in a full-scale RCT. To estimate the MCID, we will use adolescents’ global ratings of change on a 10-point Likert scale (-5 to +5), a commonly used anchor [44,45].

Satisfaction will be measured in adolescents allocated to the treatment condition at the end of module 8 (post-intervention) to infer intervention acceptability. A 12-item instrument developed by the research team will measure satisfaction based on the adolescent’s report of the program’s engagement and sense of safety/privacy, expectations and usefulness, communication, and technical (intervention) management. For 10 statements, a 5-point Likert response format ranging from strongly agree (score 5) to strongly disagree (score 1) will be used. Scores range from 10 to 50 with scores of 40 or greater indicating higher acceptability. Two open-ended questions to inform the larger trial will allow adolescents to identify challenges or barriers that were faced in taking part in the trial, and the extent to which adolescents used the skills learned.

Treatment adherence will be measured at 8 weeks to further evaluate intervention acceptability. Adherence is measured by documenting the number of treatment modules and homework tasks completed. We will also record the number of tailored modules completed by each participant (treatment arm) and site visits (control arm). These data are being collected through IRIS.

Health care resource use will be detailed for a preliminary cost-consequence analysis [46,47]. The following are being reviewed: (1) software development and maintenance costs, (2) training and personnel costs for the treatment arm, (3) health care utilization data (eg, visits to the emergency department, hospital admission), and (4) other costs reported by adolescent (ie, time off from work/school). Adolescents will be asked at the post-intervention assessment to report on the use of co-interventions during the study period (eg, emergency department visits, other treatments, medication) and reasons for this use (eg, unmet need, medication prescribed before the study).

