### Sample Size

We have been conservative in estimating our ability to enroll and retain participants, by assuming that 50% will refuse to participate and 50% of enrolled adolescents will drop out. A total of 160 adolescents are being invited to participate with the expectation that we will enroll 80 adolescents (40 assigned to each study arm) and retain 40 adolescents (20 per arm) by module 8 completion (post-intervention). In keeping with the standard goals of a pilot RCT, a sample size of 40 adolescents at post-intervention (20 per arm) will provide sufficient data on the primary outcome to calculate a sample size based on 90% power for a full-scale RCT [48,49].

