## Discussion

As current systems-based models of health care look to enhance local community resource capacity, stepped care options and improved access to mental health services for adolescents are needed. Recent systematic reviews have shown that self-led, computer-based and computer-assisted CBT are viable treatment approaches for adolescents, but suggest that maturation of the evidence base is needed [30,31,32]. This pilot RCT is an essential step to designing a robust RCT to evaluate the effectiveness of Internet-based CBT for adolescents with moderate to mild anxiety problems. As a first step, satisfaction and treatment adherence results will indicate whether we need to make any critical intervention changes prior to a full-scale RCT.

We will use our pilot RCT results to develop a protocol for a full-scale trial. This trial will be designed to test the effectiveness of the *Breathe* program compared to a web-based, minimal control intervention providing psychoeducation (static webpage) in reducing anxiety symptoms in adolescents with moderate to mild anxiety problems. The MCID, sample calculation, and co-intervention use determined from the pilot RCT will inform full-scale trial methodology. Our sample calculation will ensure the full-scale trial is adequately powered, and will address sample size limitations noted in the literature to date [30]. The use of the MCID in the full-scale trial may also help to clarify inconclusive self-rated treatment effects reported across similar trials [30]. Our cost-consequence analysis will inform a cost-effectiveness analysis in the full-scale RCT. Finally, we will use the recruitment and retention rates calculated in the pilot trial to determine the number of study sites and timeline necessary to recruit the full-scale RCT sample.

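### The satisfaction score and the barriers question are tied to the end of module 8, which the plan expects only half the Breathe arm to reach

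*Protocol article*

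**What the plan says.** Secondary Outcome Measures fixes both the population and the moment: "Satisfaction will be measured in adolescents allocated to the treatment condition at the end of module 8 (post-intervention) to infer intervention acceptability". Ten of the 12 items are scored: "Scores range from 10 to 50 with scores of 40 or greater indicating higher acceptability". The other two are open questions, one of them on challenges or barriers to taking part.

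The same section times the other acceptability measure by the calendar: "Treatment adherence will be measured at 8 weeks to further evaluate intervention acceptability". It is a count: "Adherence is measured by documenting the number of treatment modules and homework tasks completed".

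Two other places bear on the timing. Table 1 puts treatment satisfaction in the 8-week post-intervention column. The Primary Outcome Measure section writes week 8 and the end of the eighth module as a single time point for the MASC2 in the treatment group ("baseline (pre-treatment), 8 weeks/end of 8^th").

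The Sample Size section plans by "assuming that 50% will refuse to participate and 50% of enrolled adolescents will drop out", and arrives at 20 per arm at module 8 completion. The Discussion gives the use of the results: "satisfaction and treatment adherence results will indicate whether we need to make any critical intervention changes prior to a full-scale RCT".

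**The concern.** Acceptability is one of the six objectives of this pilot, and its stated purpose is to show what must change in the program before a full trial. If the instrument appears when a participant finishes module 8, those who stopped earlier do not meet it. Some of them will have stopped because the program did not suit them, or because they ran into the barriers that the open question asks about. Their answers are the most useful ones for revising the program.

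Two things are at stake. The score may be read as the view of everyone offered Breathe when it is the view of those who stayed to the end. And the reasons for stopping may go unrecorded.

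**Working it through.** **Inputs from the article.** Sample Size: 160 invited, 50% refusal, 50% dropout, 40 per arm enrolled, 20 per arm retained at module 8 completion. Secondary Outcome Measures: score range 10 to 50, mark at 40. Treatment Condition: 8 modules. Statistical Analyses: a completer has done more than 75% of modules. The article gives no satisfaction data, so every satisfaction value below is an assumption.

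**1. The plan's own figures.** Enrolled = 160 × (1 − 0.5) = 80, or 40 per arm. Retained = 80 × (1 − 0.5) = 40, or 20 per arm. Both reproduce. With the instrument given at the end of module 8, 40 − 20 = 20 of 40 Breathe participants (50%) would have no score.

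**2. The completer definition.** 0.75 × 8 = 6, so a completer has done 7 or 8 modules. Someone who stops after module 7 is a completer in the analysis but, on the literal wording of Secondary Outcome Measures, is not asked about satisfaction.

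**3. Proportion scoring 40 or more.** For the whole arm this is (finishers at 40 or more + leavers who would be) / 40. Assume 16 of 20 finishers, so the reported figure is 16/20 = 80%.
- No leaver would score 40 or more: (16 + 0)/40 = 40%.
- 16 of 20 leavers would: (16 + 16)/40 = 80%, so no bias.
- All leavers would: (16 + 20)/40 = 90%.

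**4. Mean score.** Bias = (1 − c) × (finisher mean − leaver mean), where c is the share reaching module 8. Take c = 0.5 and an assumed finisher mean of 42:

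| Assumed leaver mean | Whole-arm mean | Bias |
|---|---|---|
| 42 | 42.0 | 0 |
| 35 | 38.5 | 3.5 |
| 30 | 36.0 | 6.0 |
| 20 | 31.0 | 11.0 |

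The logical limits are (20 × 42 + 20 × 10)/40 = 26 and (20 × 42 + 20 × 50)/40 = 46. If more reach module 8, say c = 0.75, a leaver mean of 30 gives 0.75 × 42 + 0.25 × 30 = 39.0, a bias of 3.0.

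**5. What adherence recovers.** Modules and homework completed can be recorded for anyone who logged in, including early stoppers. That gives the number who stopped and when. The satisfaction items cover engagement, safety and privacy, usefulness, communication and technical matters, and the open question covers barriers. None of these can be read off a module count. The comparison of completers with non-completers in Statistical Analyses concerns characteristics such as gender; the article describes no collection of reasons for stopping.

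**The case against.** The case for the plan has real substance.

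- **Adherence is a second acceptability measure.** It is timed to 8 weeks and covers early stoppers. The Discussion bases any critical changes on satisfaction and adherence together. This stands. A reader might infer that acceptability is measured only in finishers, or that a good score could hide the loss of half the arm. The article does not support that: adherence, the retention rate and the completer comparison would all reveal heavy stopping. They would not reveal its causes.
- **The trigger may be week 8, not module 8.** The population is named as those allocated to treatment, Table 1 says 8 weeks, and the MASC2 text treats the two as one. This stands as an ambiguity. It remains open whether someone still in the study at week 8 but short of module 8 is asked. It does not settle the matter, because the satisfaction sentence names the module while the sentence on adherence names the week.
- **The direction and size of any bias are not known.** This also stands. Some adolescents stop for reasons unrelated to the program, and the bias is zero if leavers would score like finishers. The 50% dropout is a deliberately cautious planning figure, not an observed rate.
- **An article condenses the full protocol.** Administration detail may sit there. But the timing is not omitted here; it is stated, in two ways that differ.

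**Conclusion.** The point holds for the satisfaction score and the open barriers question, not for acceptability as a whole. As worded, they come from finishers, about 20 of 40 on the plan's own dropout figure, and adherence counts cannot supply the missing answers. The score is likely to be higher than for the whole arm, because dissatisfaction is a plausible reason to leave, but this is an inference. In the illustration, an observed 80% is compatible with 40% to 90% in the whole arm: up to 40 points lower, at most 10 higher.

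A reader might go further and state an overstatement of 20 to 30 percentage points. That follows only if 20% to 40% of leavers would score 40 or more (0.5 × 0.80 + 0.5 × 0.20 = 0.50; 0.5 × 0.80 + 0.5 × 0.40 = 0.60), and nothing in the article supports those values. Nor does the article set an arm-level proportion that would decide for or against changes; the mark of 40 is described only for scores, and the planned analysis is descriptive.

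The change is worth making: it protects one pilot objective at little cost, and without it the score cannot be read as the view of the arm.

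**What to change.** 1. Reconcile Secondary Outcome Measures with Table 1. State that the instrument goes to every adolescent allocated to Breathe at week 8, or at discontinuation if earlier, whatever the number of modules completed.
2. Send it by e-mail link outside the modules, with a not-reached response option for items that depend on later content.
3. Report the number responding out of all allocated, and show results by modules completed.
4. Give the proportion at 40 or more with best-case and worst-case bounds for non-responders. Present these as bounds: counting every non-responder as dissatisfied would largely restate dropout.
5. Read the score together with adherence when deciding on changes to the program.

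The cost is an automated message, minor rewording of items and a few lines of analysis. E-mail contact already exists for login details and for prompts after a week without login, and enrolment was still open when the article was written. The downside is that response among leavers may be low, but the reported denominator would then show it.

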Trained mental health professionals have traditionally delivered CBT, but the structured and sequential nature of CBT translates well to computer-based delivery. Within this approach, the use of the Internet as a delivery mode provides researchers with unobtrusive ways to capture data and examine access patterns, compliance, and usability issues [26]. Internet-based delivery also circumvents multiple barriers to receiving in-person CBT including: social stigma, direct and incidental costs (eg, time out of school), lack of trained deliverers, and inconvenient service times and locations [27]. This delivery method may also increase the number of young people seeking professional help. A published paper in 2002 reported that over a one-year timeframe, only 8.3% of young people with recent onset anxiety and 21.4% with chronic anxiety had sought professional help [28]. While Internet-based CBT is considered lower-intensity than in-person treatment, the majority of adolescents with anxiety disorders experience mild to moderate distress and impairment, making treatment availability paramount. Thus, Internet-based CBT is proposed to reduce demand for therapy delivered in-person, introduce cost savings, and increase timely access to recommended treatment [29].

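### Co-intervention use and costs are collected once, at 8 weeks, with an undefined recall window, no baseline measure, and nothing for weeks 8 to 20 in the Breathe arm

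*Protocol article*

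**What the plan says.** Objectives 5 and 6 of the pilot are to determine the use of co-interventions and to carry out a cost-consequence analysis that will inform the cost-effectiveness analysis of the full trial.

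The data for both come from one report (Protocol article, Secondary Outcome Measures): "Adolescents will be asked at the post-intervention assessment to report on the use of co-interventions during the study period". Adolescents also give reasons for that use, and medication that pre-dates the trial is one of the examples. The same section says that all secondary outcome data are self-reported through IRIS. In Table 1 the row "Co-intervention use/costs" has a single entry, at "8 weeks (postintervention"). It has none at baseline and none at "20 weeks (3-month follow-up").

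The anxiety score follows a longer schedule, and this differs by arm. Under Primary Outcome Measure, the treatment group completes the MASC2 at baseline, at "8 weeks/end of 8^th" module, and at "3 months post-treatment (follow-up"). For the other arm the text says: "Adolescents in the control group complete the MASC2 at baseline and 8 weeks after study enrolment via IRIS". Table 1 and the abstract show the 3-month follow-up without separating the arms.

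The economic rationale is in the Introduction: "Internet-based CBT is proposed to reduce demand for therapy delivered in-person, introduce cost savings".

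**The concern.** Three things are loosely fixed.

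- **Recall window.** A question put at week 8 cannot report on a study period that runs beyond week 8, and the article does not say where that period ends. The treatment arm's assessment is tied to week 8 or the end of module 8, and the control arm's to 8 weeks after enrolment. Without a stated window, the two arms could report on intervals of different length.
- **No baseline.** Participants enter while seeking care from emergency departments, crisis teams or primary care, so some will already be using services or medication. The plan recognises this by asking for reasons, but a reason recalled at week 8 is the only means of telling continuing use from new use. With about 20 per arm expected at that point, a chance imbalance in prior use could move mean costs noticeably.
- **Nothing after week 8.** The Breathe arm is contacted again at 20 weeks, but resource use is not asked about then. The pilot therefore cannot help to judge whether 8 weeks is a long enough costing horizon for the full trial. Nor can the 20-week MASC2 scores in that arm be described alongside therapy or medication begun after week 8.

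Two of the six stated objectives depend on these data, and use that was not asked about is hard to recover later.

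**Working it through.** **Inputs (Protocol article).** Post-intervention assessment at 8 weeks and follow-up at 20 weeks (Table 1). MASC2 to 20 weeks in the treatment arm and to 8 weeks in controls (Primary Outcome Measure). 160 invited, 50% refusal, 50% dropout, 40 enrolled per arm (Sample Size).

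**The plan's own figures.**
- Follow-up time: 8 weeks + 3 × 4 weeks = 20 weeks, as in Table 1. With calendar months it is 8 + 13.0 = 21.0 weeks, a rounding difference only.
- Sample: 160 × 0.5 = 80 enrolled; 80 × 0.5 = 40 retained, or 20 per arm. Both reproduce.

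**Weeks without resource-use data**, taken as scheduled MASC2 follow-up minus the 8 weeks that the single report can cover:

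| | Scheduled weeks | Covered | Uncovered |
|---|---|---|---|
| Breathe arm | 20 | 8 | 12 (12/20 = 60%) |
| Control arm | 8 | 8 | 0 |
| Both, equal arms | 28 | 16 | 12 (12/28 = 43%) |

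In person-weeks at 40 per arm: scheduled 40 × 20 + 40 × 8 = 1120; uncovered 40 × 12 = 480; 480/1120 = 43%. At 20 per arm it is 240/560, the same share.

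**Sensitivity to the reading of Table 1.** If both arms were followed to 20 weeks, the uncovered share would be (2 × 40 × 12)/(2 × 40 × 20) = 60%. That reading goes against the text of Primary Outcome Measure.

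**Randomised comparison.** The only change-score estimate in Statistical Analyses runs from baseline to post-intervention. Uncovered weeks within it: 8 − 8 = 0.

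**Before enrolment.** Weeks of service use measured before enrolment: 0 in either arm.

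**The case against.** The case for leaving the schedule alone is fair in several respects.

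- A question asked at week 8 about the study period reads most naturally as enrolment to week 8. That matches the 8-week intervention and control periods and the only planned change-score comparison. This stands as a likely intention, but it is not written down.
- After week 8 controls may take up Breathe, so later cost data could not give a clean randomised contrast. This stands, and it limits any use of weeks 8 to 20 to description.
- Randomisation makes prior use similar on average, and the reasons question partly deals with continuing use. This stands in part. Similarity on average gives limited protection with about 20 per arm, and a recalled reason is a weaker tool than a baseline report.
- The cost analysis is called preliminary, and the costing horizon is a matter for the full trial. This stands, but informing that trial is the stated purpose of the analysis.

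A reader might also infer more than the documents support:

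- **That 60% of all follow-up lacks cost data.** The text gives the 20-week assessment to the treatment group only, so 60% applies to that arm alone.
- **That the whole cost of the intervention is set against 8 weeks of service use.** Statistical Analyses spreads the investment cost over 3 to 5 years, with a 5% rate and sensitivity analyses at 3% and 0%.
- **That early use mostly belongs to the care-seeking episode and that savings come later.** This is plausible, but the article gives no figure or timing for it.

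**Conclusion.** The point holds as a specific weakness of data collection. It is not a flaw in the randomised comparison. Resource use has one collection point, its window is undefined, and nothing is measured at baseline in either arm. In the Breathe arm 12 of 20 scheduled weeks are uncovered; across equal arms it is 12 of 28 (43%). No week of the 8-week between-arm comparison is missed.

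This rests on three assumptions: the text of Primary Outcome Measure, rather than the undivided Table 1, governs who is followed to 20 weeks; arms are equal in size, as planned; and there is no other source of utilisation data for weeks 8 to 20. On the last, the article lists health care utilisation among the items under review without giving its timing, but the statement that secondary outcomes are self-reported in IRIS and the single entry in Table 1 both point the same way.

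The change is worth making because it is cheap and serves two stated objectives. Leaving it unmade would not invalidate the pilot.

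**What to change.** In Secondary Outcome Measures and Table 1:

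1. Define the week-8 recall window as enrolment to week 8, in the same words for both arms.
2. Add the existing co-intervention and cost questions at baseline in both arms, over a pre-enrolment window of fixed length. Use the answers to describe, or adjust, the between-arm cost comparison for weeks 0 to 8. Do not report them as an uncontrolled before-after change: participants enroll while seeking care, so a fall from that window would largely reflect regression to the mean.
3. Add the same questions at the Breathe arm's existing 20-week IRIS contact, covering weeks 8 to 20, and report them descriptively to inform the full trial's costing horizon.
4. Reconcile Table 1 and the abstract with the text on which arms are followed to 20 weeks. If controls are contacted then, report their use split by whether they took up Breathe.

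The cost is a slightly longer online questionnaire at baseline in both arms and at 20 weeks in the Breathe arm. No new visit or contact is needed, because both online contacts already exist. Contacting controls at 20 weeks would be an addition under the current text, and this fix does not depend on it.
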